### Sample Size

In previous studies with face-to-face group MBCR, we have observed medium effects for symptoms of stress (measured by the Calgary Symptoms of Stress Inventory [C-SOSI]) as the primary outcome and expect similar effects in this study. Also, recent meta-analyses of MBIs and psychosocial stress outcomes have demonstrated a similar medium standardized effect size of Cohen *d*=0.5 for stress [34]; also, most MBI studies collect their primary outcome at 3 months postbaseline as most mindfulness interventions span 6 to 10 weeks [7,34]. For this study, we therefore used a medium effect size (*f*=0.25) to conduct an a priori sample size calculation using the software G*Power 3.1.9.3 developed and maintained by researchers at Heinrich Heine University Düsseldorf [35]. The other parameters for estimating the sample size included, a standard type-1 error rate, α=.05, and a low risk of type-2 error, power (1-β)=.95, to detect interaction effects between time points (baseline and 3 months postbaseline) and group (intervention and control) using a repeated measures analysis of variance with correlation among repeated measures assumed to be 0.5 and nonsphericity correction ε=1. The total required sample size reported by G*Power was 54 participants to detect such an interaction effect.

In addition, based on our previous experience with online and in-person MBI trials and previous app-based studies [10,18,20,34,36], we assumed approximately 20% attrition and 10% to 15% probability of missing data. Therefore, we oversampled for this study accordingly. Hence, the final total sample size we aim to recruit in this study is N=74, with n=37 in the immediate intervention arm and n=37 in the waitlist control arm. Please refer to Figure 2 for the study flowchart that describes estimated sample size calculations at each assessment.

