### Randomization

Participants will be randomized by the study statistician, by generating participant ID numbers and group allocations for the entire study in advance using a random number generator program in SPSS. Block lists of randomized participant IDs will then be uploaded to the Research Electronic Data Capture (REDCap) randomization module, which will allow the study staff to provide immediate group allocation to participants after completion of consent procedures. Only the study statistician will develop the group assignments, which are locked by REDCap after upload, to prevent selection bias. Randomization will occur after the baseline assessment, and those in the immediate *Am* MBCS intervention group will get a text message and email containing the link to download the *Am Mindfulness* app, from the Android or Apple app store. The waitlist control group will be informed that they will need to wait for the intervention and will be contacted when they can download the *Am*
*Mindfulness* app and start the intervention.

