### Descriptive Statistics

Data will be cleaned, the descriptive statistics of the sample will be assessed, and all variables will be checked for normality of distribution. Descriptive statistics of our sample will be calculated to summarize demographic and disease-related characteristics and check for group differences between groups using Chi-squared and *t* tests. In case data are nonnormal, the Kenward-Roger correction for degrees of freedom will be applied to the LMM. Potential treatment moderators of age, sex, cancer type, cancer stage, and chemotherapy regimen will also be included as possible covariates. We will also conduct correlation and regression analyses to determine correlations between scores of the primary and secondary outcome measures, eg, correlation between C-SOSI and PROMIS-Cancer Anxiety scores, and between secondary outcome measures, eg, correlation between PROMIS-Cancer Fatigue scores and mood words selected by the participant in the *Am* app.

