### Hypothesis Testing

#### Hypothesis 1

LMM is a suitable statistical method for this study because of the ability to perform sophisticated statistical imputation of data missing at random in a longitudinal study design. In addition, the LMM also includes mixed effect methods with a random intercept model, which can account for the variances between participants and within participants. Therefore, we plan to use the LMM analyses for testing hypotheses 1 and 2, wherein the LMM will estimate differences between the immediate group and waitlist control group by conducting a group × time interaction analysis with a significance level of α<.05. Each of the LMMs will include fixed effects for time (within-subjects factor) and group (between-subjects factor) and a random effect for the participant. Also, the restricted maximum likelihood estimate method in the LMM will be used to estimate the model parameters and standard errors with a compound symmetry covariance structure to account for the correlation between measurements. Data for testing hypothesis 1 will be C-SOSI total scores and subscale scores for 3 months postbaseline. Within- and between-group differences for the immediate and waitlist groups revealed by the LMMs will be reported with respective *P* values and the specific model effects, *F* (*df*).

#### Hypothesis 2

Similar to hypothesis 1, for hypothesis 2, we will use the same LMMs to test for within- and between-group differences for the secondary outcomes.

#### Hypothesis 3

For hypothesis 3, linear and curvilinear multiple regression models will be used, along with simple Pearson correlations to detect associations between the primary and secondary self-reported outcomes and the exploratory outcomes obtained from the app data.

#### Hypothesis 4

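### The primary interaction test is valid but amounts to a change-score comparison, and it gives up about 19–25% of the information that the pre-randomisation baseline could supply at the plan's own correlation of 0.5

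*Protocol article*

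**What the plan says.** Hypothesis Testing (Hypothesis 1) specifies a linear mixed model fitted by REML with compound symmetry: "Each of the LMMs will include fixed effects for time (within-subjects factor) and group (between-subjects factor) and a random effect for the participant". The test is the group × time interaction, and Hypothesis 2 reuses the same model for the secondary outcomes.

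The Sample Size section identifies the time points. The calculation was made "to detect interaction effects between time points (baseline and 3 months postbaseline) and group (intervention and control", with the "correlation among repeated measures assumed to be 0.5".

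The Randomization section fixes the order of events: "Randomization will occur after the baseline assessment".

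The only covariates named are in Descriptive Statistics: "Potential treatment moderators of age, sex, cancer type, cancer stage, and chemotherapy regimen will also be included as possible covariates". The baseline score of the outcome is not among them, and the article nowhere sets the two arms to a common baseline mean.

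**The concern.** With baseline and 3 months as the two levels of time, and the group effect left free at baseline, the interaction is the difference between arms in mean change from baseline. That contrast subtracts the whole baseline difference between arms, which is the same as assuming a slope of 1 on baseline, whereas the plan's own correlation implies a slope of 0.5 (equal variances).

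Randomisation after the baseline assessment makes the expected baseline difference zero. A model that estimates it anyway uses up information. What is at stake is the width of the interval and the power of the primary test and of every secondary test that uses the same model. The data needed to recover the loss are already collected.

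**Working it through.** **Inputs.** From Sample Size: α = 0.05, power 0.95, f = 0.25, correlation ρ = 0.5, ε = 1, required N = 54, target N = 74 (37 per arm), about 20% attrition and 10–15% missing data. From Hypothesis Testing: compound symmetry. The outcome SD is taken as 1 at each visit.

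**1. The plan's own figure.** For the within-between interaction with two time points and two groups, λ = f²·N·m/(1−ρ) = 0.0625 × 54 × 2/0.5 = 13.5 on 1 and 52 df. Power is 0.950; N = 52 gives 0.942. So N = 54 reproduces.

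**2. What that test is.** The SD of a change score is √(2(1−ρ)) = 1.0. With 27 per arm, the SE of the difference in change is √(4/54) = 0.272. The noncentrality is √13.5 = 3.674, so the effect being powered is 3.674 × 0.272 = 1.0 SD. A t test on change scores with this difference has the same power, 0.950. The planned interaction is therefore the change-score comparison.

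**3. Information lost, complete data.** Variance factor of the 3-month effect:
- planned (change score): 2(1−ρ) = 1.00
- baseline-adjusted: 1−ρ² = 0.75
- ratio: (1+ρ)/2 = 0.75

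The loss is 25% on the information scale. The planned SE is 1/√0.75 = 1.155 times as large. Across ρ, the ratio is 0.65 at 0.3 (35% lost) and 0.85 at 0.7 (15% lost). The generalised least squares information matrix under compound symmetry gives 0.75 with two visits and also with four (baseline, 2 weeks, 4 weeks, 3 months).

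**4. Information lost with missing 3-month data.** Combining 20% attrition with 10% or 15% missing gives 1 − 0.8×0.9 = 28% or 1 − 0.8×0.85 = 32%. With two visits, the ratio of the common-baseline model to the planned model is 0.75/(0.75 + 0.25(1−m)), where m is the proportion missing:

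| Missing at 3 months | Two visits | Four visits |
|---|---|---|
| 28% | 0.806 (19.4% lost) | 0.799 (20.1% lost) |
| 32% | 0.815 (18.5% lost) | 0.807 (19.3% lost) |

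So the loss is about 19–20%.

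**5. Power with 54 completers, ρ = 0.5** (noncentral t; 52 df planned, 51 df adjusted):

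| True 3-month effect | Planned | Baseline-adjusted |
|---|---|---|
| 1.0 SD (the effect in the calculation) | 95.0% | 98.6% |
| 0.5 SD (the cited d) | 43.8% | 54.8% |

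Simulation at 0.5 SD gives 44% and 54%. For 0.5 SD, the 95% interval half-width falls from 0.55 to 0.47 SD. For the 1.0 SD effect, 95% power would need 42 participants with adjustment in place of 54. Simulated type I error is 4.9% for both analyses.

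**The case against.** The strongest reply is that nothing here is an error. In a randomised trial the interaction test is unbiased with correct type I error, and the 54 participants were computed for that same test. All of this stands. A reader might infer that the primary test is biased, or that the sample size is wrong on this account; the documents support neither.

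A reader might also take the 25% as the loss to expect. It holds only for complete data, and the plan itself expects missing data.

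The rise from 44% to 54–55% might be read as the cost of the model choice, or as a rescue of power. It is neither. The low starting value arises because f = 0.25 in this procedure is a 1.0 SD difference in change and not the cited d = 0.5. That is a separate sample-size matter, which adjustment does not repair. At the powered effect, the gain is 3.6 points.

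Chance imbalance might look like a second harm. At N = 74 a one-SE baseline imbalance is √(4/74) = 0.23 SD and moves the change-score estimate by 0.5 × 0.23 = 0.12 SD. That shift is part of the extra variance already counted.

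Finally, the text is not fully explicit. Hypothesis 1 describes its data as 3-month scores, and the covariate list is of possible covariates. But a time factor needs more than one visit, and Sample Size names the two. Even a comparison of 3-month scores alone has variance factor 1.00, so at ρ = 0.5 with complete data the loss against adjustment would again be 25%. An unseen analysis plan could add baseline adjustment, but the article states the model terms, the test and the covariance, and that stated model is the inefficient one.

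**Conclusion.** The point holds as one of efficiency. The model stated for Hypotheses 1 and 2 gives up 25% of the available information at ρ = 0.5 with complete data, and about 19–20% at the missingness the plan expects. The complete-data range is 15% to 35% for ρ from 0.7 to 0.3.

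This rests on reading Hypothesis Testing together with Sample Size, on equal variances and compound symmetry, and on the 3-month-versus-baseline contrast being the one of interest. If more visits enter the model, the overall interaction becomes a test on several degrees of freedom, and only that contrast is the change-score comparison.

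The change is worth making because it is almost free. It is not needed for the validity of the trial.

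**What to change.** In Hypothesis Testing, for Hypotheses 1 and 2, keep the baseline score in the outcome vector, drop the group effect at baseline so that both arms share one baseline mean, and name the group contrast at 3 months as the test.

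A second choice is to enter the baseline score of the same outcome as a covariate and model post-baseline visits up to 3 months. It is nearly but not fully equivalent: it drops participants who have only a baseline score, whereas the Intent-to-Treat Analysis section includes everyone who entered the study. The common-baseline model therefore fits the plan better.

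The cost is a sentence or two of analysis text and a small change to the model, with no new data, visits or participants. The covariate form uses one degree of freedom. Because the trial is open-label and the Results section reports enrolment complete, the change needs a dated, justified amendment made before outcome data are analysed by arm.

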**Primary outcome**			
	Symptoms of stress	Calgary Symptoms of Stress Inventory (C-SOSI) [47]	The C-SOSI is a 56-item scale, derived from exploratory factor analysis on the 95-item Symptom of Stress Inventory (SOSI) collected from cancer patients who attended our MBCS program. A 5-point scale (“never” to “very frequently”) is used to rate the frequency of stress-related symptoms in the past week. There is a total score and 8 subscales (depression, anger, muscle tension, cardiopulmonary arousal, sympathetic arousal, neurological or GI, cognitive disorganization, and upper respiratory symptoms), all of which have high internal consistency (0.80 to 0.95), and the total score has good convergent and divergent validity with other well-validated measures.

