### Objectives and Hypotheses

#### Objective 1: Primary Outcome

The first objective is to evaluate the efficacy of the *Am* app–based MBCS program to relieve symptoms of stress (primary outcome).

*Hypothesis 1:* Compared with controls, the *Am* app–based MBCS program participants will report significantly less symptoms of stress at 3 months postbaseline (primary outcome) assessment.

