#### Objective 2: Secondary Outcomes

The second objective is to evaluate the efficacy of the *Am* app–based MBCS program to decrease the fear of cancer recurrence, anxiety, depression, and fatigue, and to improve overall physical functioning (secondary outcomes) at 3 months postbaseline assessment.

*Hypothesis 2:* Compared with controls, the *Am* app–based MBCS program participants will report significantly less fear of cancer recurrence, rumination, experiential avoidance, anxiety, depression, and fatigue, and increased mindfulness and overall physical functioning at 3 months postbaseline (secondary outcomes).

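### The single primary hypothesis is assigned nine C-SOSI scores at an unadjusted .05, and the article does not say which score decides it

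*Protocol article*

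**What the plan says.** All references are to the protocol article.

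- **Objectives and Hypotheses, Objective 1.** There is one primary hypothesis, on one construct at one time point: app participants "will report significantly less symptoms of stress at 3 months postbaseline (primary outcome) assessment". The deciding score is not named.
- **Outcome Measures, Table 3, primary outcome.** The instrument is the C-SOSI. "There is a total score and 8 subscales", which makes nine scores. None is singled out as the endpoint.
- **Hypothesis Testing, Hypothesis 1.** The plan is a linear mixed model with a "group × time interaction analysis with a significance level of α<.05". The same section then says: "Data for testing hypothesis 1 will be C-SOSI total scores and subscale scores for 3 months postbaseline". Total and subscales stand side by side. The subscales are not called supportive or exploratory, and no adjustment is given.
- **Sample Size.** The calculation is for one group-by-time interaction, with "a standard type-1 error rate, α=.05" and "a low risk of type-2 error, power (1-β)=.95", and gives 54 participants.

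**The concern.** The model has fixed effects for time and group and a random effect for participant. Nothing in it distinguishes one score from another, so nine scores mean nine models and nine interaction tests, each at .05. The sample size section plans one.

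If the total is null and one subscale (muscle tension, say) reaches P<.05, a reader cannot tell from the article whether Hypothesis 1 has been supported. The authors could say yes and point to the published sentence. The trial is open-label and its primary outcome is self-reported, so a decision rule fixed in advance is one of the few protections against selecting the favourable score afterwards.

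**Working it through.** **1. The plan's own figure.** Inputs from Sample Size: f = 0.25, α = .05, power .95, two time points (m = 2), correlation ρ = 0.5, ε = 1, two groups. For a within-between interaction:

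λ = f² · N · m / (1 − ρ), with df = (1, N − 2).

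At N = 54: λ = 0.0625 × 54 × 2 / 0.5 = 13.5 with df (1, 52), and power is 0.950. At N = 52, power is 0.942. The stated 54 is reproduced, and it is the size for exactly one test at .05.

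**2. Number of tests.** 1 total + 8 subscales = 9.

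**3. Error rate under each possible decision rule, if the app has no effect.** The article does not give the correlation between subscales. The 0.80 to 0.95 in Table 3 is internal consistency, which is a different quantity. I therefore varied the correlation r from 0 to 0.9. Assumptions: eight equally correlated null statistics with equal variance; a total equal to their sum; each score tested two-sided at .05 (critical value 1.96); 1,000,000 draws per value of r.

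| Assumed r | Any of 9 significant, two-sided | Any of 9 significant in favour of the app |
|---|---|---|
| 0 | 35.2% | 19.1% |
| 0.3 | 30.2% | 15.3% |
| 0.5 | 25.1% | 12.5% |
| 0.7 | 19.1% | 9.6% |
| 0.8 | 15.8% | 7.9% |
| 0.9 | 11.9% | 6.0% |

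The reference levels are 5% for the two-sided column and 2.5% for the one-directional column.

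The other two rules, from the same simulation:

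- only the total decides: 5.0% at every r;
- all nine must be significant: below 1.5% at every r tried.

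**4. The independence formula.** 1 − 0.95⁹ = 0.370. This needs nine independent tests, which is impossible if the total is the sum of the other eight. Under that assumption the ceiling is the 35.2% in the first row.

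**5. Power under the two coherent choices.**

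- Total only, α = .05: power 0.950 at N = 54.
- Nine co-equal claims with Bonferroni, α = .05/9 = 0.0056: power 0.778 at N = 54 and 0.921 at N = 74. Reaching 0.95 takes 82 evaluable participants, which is more than the recruitment target of 74.

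**The case against.** The strongest reply is that the article nowhere says one significant subscale is enough. It has one hypothesis on one construct at one time point, and a sample size for one test. Both fit the reading that the total decides, under which the error is 5% and nothing is wrong with N. A condensed article may also leave multiplicity rules to a statistical analysis plan that is not shown.

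Much of this stands. A reader might infer that the primary claim simply has a false-positive rate of 19% to 37%. The article does not support that. The inflation needs the any-score rule, which is not stated. The 37% end needs independence that a summed total rules out. The 19% end is only the value at r = 0.7, and higher correlations give less. The two-sided rates also count results where the app looks harmful, which could not support a directional hypothesis.

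A reader might also extend the point to Hypothesis 2, which lists eight outcomes at .05. That does not follow. Those outcomes are separate constructs, each named and labelled secondary, and whether to adjust them is a trade-off commonly left to the analysis plan.

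The reply does not remove the sentence on Hypothesis 1. The article is not silent there: it says which data test the primary hypothesis, and the subscales are among them. An analysis plan in which the total alone decides would have to narrow that published statement.

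**Conclusion.** The point holds for Hypothesis 1, in conditional form. The article assigns nine scores to one confirmatory hypothesis at an unadjusted .05, with no order and no rule for when the hypothesis is supported, while the trial is sized for one test.

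The familywise error is 5% if only the total decides and about 12% to 35% two-sided if any score may count. For results favouring the app, the any-score figure is about 6% to 19% against 2.5%. Which applies cannot be read from the text. The ranges rest on assumed equal subscale correlations between 0.9 and 0 and on a total that is the sum of the subscales; the article gives neither. At every correlation tried, the any-score rule more than doubles the nominal rate.

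**What to change.** Replace the sentence on the data for Hypothesis 1 with:

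*Hypothesis 1 is tested once, on the C-SOSI total score at 3 months postbaseline, at two-sided alpha .05; the 8 subscales are supportive and reported as estimates with 95% CIs.*

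The analysis plan should carry the same wording, fixed before the 3-month data are analysed.

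The cost is a wording change. No new data and no change in sample size are needed: N = 54 keeps power 0.95 for the single test on the plan's own inputs. The only loss is that a subscale alone can no longer support the primary claim.

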**Methods:**

This is a randomized waitlist-controlled trial, which will evaluate the effectiveness of *Am* MBCS for impacting the primary and secondary outcomes in cancer survivors who have completed all their cancer treatments. Outcomes will be assessed using web-based surveys with validated psychometric instruments at (1) baseline, (2) mid-intervention (2 weeks later), (3) immediately postintervention (4 weeks), (4) 3 months postbaseline, (5) 6 months postbaseline, and (6) 12 months postbaseline. The waitlist group will complete all assessments and will cross over to the intervention condition after the 3-month assessment. In addition, data will be obtained by the smartphone app itself, which includes users’ engagement with the app-based intervention, their emotional state (eg, angry and elated) from a user-inputted digital emotion-mapping board, and psychobiometric data using photoplethysmography technology.

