## Methods

### Study Design

The study is a two-armed randomized waitlist-controlled design with 1:1 allocation to treatment (immediate *Am* MBCS app group) or control (waitlist usual care) arms, with assessments at six time points: (1) baseline, (2) mid-intervention (2 weeks later), (3) immediately postintervention (4 weeks), (4) 3 months postbaseline, (5) 6 months postbaseline, and (6) 12 months postbaseline. A detailed study flowchart is shown in Figure 2. This is an open-label trial, as blinding to interventions is most often not possible in psychosocial intervention research.

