#### Waitlist Control Group

Participants will receive treatment as usual, followed by a delayed (waitlist) intervention of the same *Am* MBCS app-based intervention after the 3-month postbaseline assessment of the *Am* app intervention group (see Figure 2). Control group participants will get access to the *Am* app only after completing their 3-month waiting period.

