	Physical Function	PROMIS-Cancer Bank v1–Physical Function [55]	PROMIS-Physical Function instruments measure self-reported capability rather than actual performance of physical activities. This includes the physical functioning, mobility as well as instrumental activities of daily living, such as running errands. The PROMIS-Cancer Physical Function has items specific to cancer patients and survivors. The PROMIS-Cancer Physical Function item bank contains a total of 45 items, 33 of which are also in the PROMIS-Physical Function item bank [55], and will be delivered to patients in this study. The PROMIS-Cancer Physical Function has demonstrated high internal consistency (Cronbach α>.9).
	Return to work	Employment, hours of paid work, ability to work, and rate of return-to-work at 12-months	Self-reported work status will be assessed at each time point including (1) current working status (working full-time; part-time; retired; short- and long-term disability; unpaid homemaker); (2) weekly hours of paid work; and (3) job type using a well-established job classification system. If applicable, participants will be asked at follow-up on what date they returned to paid work.

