#### Objective 3: Exploratory Outcomes

This includes the exploratory aims as follows: (1) to explore correlations between the self-reported outcome data and the psychobiometric data collected by the *Am* app, (2) to determine changes over time between the *Am* app–based MBCS program and the waitlist control group.

*Hypothesis 3:* Self-reported data obtained from all participants will significantly correlate with the app-based self-reported stress data and biometric stress data.

*Hypothesis 4*: To determine the short-term, medium-term, and long-term effects of the *Am* app–based MBCS program with regard to the primary and secondary outcomes collected at all time points.

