### Intent-to-Treat Analysis

Data related to recruitment, participation, and dropout rates will be reported according to the guidelines given by the CONSORT-eHealth statement [43]. All participants that entered our study will be included in our analyses and will be retained in the arm (treatment or control) to which they were originally randomly allocated. This study will employ an ITT analysis design, wherein participants who were nonadherent to the protocol will be included in statistical analyses, regardless of their alignment with the inclusion criteria, the treatment they received, and if they withdrew from the intervention protocol (attrition) completely or deviated from the protocol (nonadherence).

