The short-term (2 weeks and 1 month postbaseline), medium-term (3 and 6 month postbaseline), and long-term (6 and 12 month postbaseline) longitudinal changes in the primary and secondary outcomes will be determined using the LMM quadratic model regressions. To account for the correlation between measurements, the restricted maximum likelihood estimate method in LMM will be used to estimate the model parameters and standard errors with a compound symmetry covariance structure. In addition, analyses with data nesting within participants will also be conducted that will control for the invariant part of each participant’s scores. The LMM regression weights (β) as well LMM regression coefficients will be reported along with a quadratic regression graph including all time points of data collection.

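### Exploratory Hypothesis 4 seeks app effects at 6 and 12 months, when the waitlist arm has also had the app and no untreated control remains

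*Protocol article*

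**What the plan says.** **Design.** Study Design sets six assessments: baseline, 2 weeks, 4 weeks, then "4) 3 months postbaseline, (5) 6 months postbaseline, and (6) 12 months postbaseline". The abstract's Methods paragraph states: "The waitlist group will complete all assessments and will cross over to the intervention condition after the 3-month assessment". The Waitlist Control Group section agrees: "Control group participants will get access to the *Am* app only after completing their 3-month waiting period".

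**Aim.** Under Objective 3 (exploratory), the second aim is "to determine changes over time between the *Am* app–based MBCS program and the waitlist control group". Hypothesis 4 is framed as "To determine the short-term, medium-term, and long-term effects of the" app programme, on the primary and secondary outcomes, at every time point.

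**Analysis.** The Hypothesis 4 text under Hypothesis Testing takes 2 weeks and 1 month as short term, 3 and 6 months as medium term, and 6 and 12 months as long term. It says that "long-term (6 and 12 month postbaseline) longitudinal changes in the primary and secondary outcomes will be determined using the LMM quadratic model regressions", using restricted maximum likelihood and compound symmetry, and promises a quadratic graph that covers all visits. It mentions no crossover term, no re-alignment of the waitlist arm to app access, and no statement that the later results are uncontrolled. The Limitations section does not raise the matter either.

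**Related text.** The Intent-to-Treat Analysis section says that participants "will be retained in the arm (treatment or control) to which they were originally randomly allocated". Table 3 lists "rate of return-to-work at 12-months" among the return-to-work measures, under secondary outcomes.

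**The concern.** The stated target and the design do not fit together after month 3. An effect of the app needs a comparison with people who do not have it, and from month 3 there are none.

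The practical risk is misreading. If the app works and its benefit lasts, the waitlist arm should catch up, and the between-arm difference at 6 and 12 months should shrink toward zero. Read as an app effect, that looks like fading benefit. If within-arm change is reported instead, it mixes any app effect with natural recovery after treatment, regression to the mean and selective dropout.

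There is a second, conditional problem of functional form. A single quadratic per arm is smooth. It cannot follow a rise over 4 weeks, a plateau, and then a step in one arm after month 3. The fit would carry post-crossover data back into the earlier part of the Hypothesis 4 curve, including its value at 3 months.

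**Working it through.** **1. The plan's own figure.** The Sample Size section gives N = 54 for the group-by-time interaction between baseline and 3 months, with f = 0.25, α = 0.05, power 0.95, correlation ρ = 0.5 and ε = 1. With m = 2 measurements, the noncentrality is λ = f²·N·m/(1 − ρ) = 0.0625 × 54 × 2/0.5 = 13.5. With 1 and 52 degrees of freedom the power is 0.950 (N = 52 gives 0.942), so 54 reproduces. It supports the 3-month contrast only; no figure is given for Hypothesis 4.

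**2. What each arm has received at each visit (from Study Design and Waitlist Control Group).**

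| Visit (months) | Immediate arm | Waitlist arm | Between-arm contrast |
|---|---|---|---|
| 0 | none | none | balance at baseline |
| 0.5, 1, 3 | app | none | app versus no app |
| 6 | app, 6 months since access | app, about 3 months since access | immediate versus delayed |
| 12 | app, 12 months since access | app, about 9 months since access | immediate versus delayed |

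This step needs no assumption about the model. The 6-month half of the medium term and all of the long term lack an untreated control. The 3-month half of the medium term is still controlled.

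**3. What a quadratic by arm over six visits would return.** Take complete, balanced data, compound symmetry and a separate intercept per arm. The mixed model's expected between-arm difference is then the ordinary least-squares projection of the visit-wise differences d onto 1, t and t²: fitted = X(XᵀX)⁻¹Xᵀd, with t = 0, 0.5, 1, 3, 6, 12 months.

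The row of that matrix for the fitted value at 3 months is 0.034, 0.101, 0.162, 0.342, 0.428, −0.067. The 6-month, post-crossover visit thus has more weight (0.428) than the 3-month visit itself (0.342).

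Assumed profile, in SD units with positive meaning benefit: the immediate arm gains 0.25 at 2 weeks and 0.50 from 1 month to 12 months; the waitlist arm is flat to month 3. The size of 0.5 matches the d in the Sample Size section. What varies is how far the waitlist arm catches up.

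| Waitlist after month 3 | | 0 | 0.5 | 1 | 3 | 6 | 12 |
|---|---|---|---|---|---|---|---|
| Full catch-up | true | 0 | 0.25 | 0.50 | 0.50 | 0 | 0 |
| | fitted | 0.25 | 0.26 | 0.27 | 0.28 | 0.24 | −0.04 |
| Half catch-up | true | 0 | 0.25 | 0.50 | 0.50 | 0.25 | 0.25 |
| | fitted | 0.22 | 0.25 | 0.28 | 0.37 | 0.42 | 0.22 |
| No crossover | true | 0 | 0.25 | 0.50 | 0.50 | 0.50 | 0.50 |
| | fitted | 0.19 | 0.24 | 0.29 | 0.46 | 0.60 | 0.48 |

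Check of the 3-month value with full catch-up: 0.101 × 0.25 + 0.162 × 0.50 + 0.342 × 0.50 = 0.025 + 0.081 + 0.171 = 0.277, a shortfall of (0.50 − 0.277)/0.50 = 45%. Half catch-up adds 0.25 × (0.428 − 0.067) = 0.090, giving 0.367. No crossover adds 0.50 × 0.361 = 0.181, giving 0.458.

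So the quadratic form alone costs about 0.04 at 3 months (0.50 to 0.46), and full crossover takes it down by a further 0.18. The false baseline difference comes mostly from the quadratic form: it is already 0.19 without crossover.

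**4. Other assumptions, all with full catch-up.** The fitted 3-month value is 0.24 with waning in the immediate arm, 0.24 if that arm improves more slowly, and 0.40 if time is coded as visit number 0 to 5. Across all crossover cases tried, including half catch-up, the range is 0.24 to 0.40 against a true 0.50. With time as a factor, or with visits through month 3 only and time as a factor, the expected value is 0.50.

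**The case against.** A good deal of the case on the other side stands.

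- *The main results are safe.* Hypotheses 1 and 2 are fixed at 3 months, before crossover, and tested in a separate group-by-time model with time as a factor. A reader might infer from the figures above that the trial's main 3-month estimate is biased. The document does not support that; the distortion could touch only the exploratory Hypothesis 4 curve.
- *The model by arm is inferred.* The Hypothesis 4 text names neither group nor an interaction, and part of it reads as within-person analysis. The comparison by arm comes from the second exploratory aim. If group is left out, however, the curve pools treated and untreated time in the waitlist arm, which is no better. If only within-arm change is meant, the missing label remains.
- *One curve through all visits is also inferred.* All visits are mentioned for the graph. The text names three windows and regressions in the plural. A quadratic through baseline plus the two visits of a window would be saturated, and nothing would leak between windows. The leakage in steps 3 and 4 is therefore conditional; the missing control in step 2 is not.
- *Return to work.* A reader might infer a planned 12-month between-arm test. None is stated: Table 3 lists the measure, and neither Objective 2 nor Hypothesis 2 names it.
- *Intention to treat.* Keeping participants in their randomised arm is correct and is no fault here. It preserves immediate versus delayed access; it does not turn that into app versus no app.
- *A condensed article.* Modelling detail may sit in a fuller document. But the article itself states the target, the comparator, the visits and the functional form, and these conflict with its own design.

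**Conclusion.** The point holds for exploratory Hypothesis 4. At 6 and 12 months the trial has no untreated control, so the medium-term result at 6 months and every long-term result cannot be an effect of the app against the waitlist. This follows from the document alone.

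The loss at 3 months on the Hypothesis 4 curve (0.28 or 0.37 in place of 0.50, against 0.46 without crossover) is an illustration. It rests on an assumed 0.5 SD lasting benefit, on assumed catch-up, on complete data, and on a quadratic fitted by arm over all six visits. If that model is used, Hypothesis 4 would publish a second 3-month estimate at odds with the one from Hypothesis 1.

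The 3-month primary and secondary analyses are unaffected, and month 3 within the medium term remains a valid randomised comparison.

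**What to change.** In the Hypothesis 4 text:

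1. Limit app-versus-waitlist inference to visits from baseline through month 3, with time as a factor.
2. Report the 6- and 12-month results as immediate versus delayed access, or as within-arm change labelled uncontrolled. Alternatively, model the waitlist arm by time since app access (month 3 as its new baseline, months 6 and 12 as 3 and 9 months after access) in place of one quadratic by randomised arm across the crossover.
3. Reword the second exploratory aim and Hypothesis 4 so that effects against the waitlist control are claimed only up to month 3.
4. Treat any 12-month return-to-work rate in the same way, as descriptive or as immediate versus delayed.

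This changes wording and model only; no new data or visits are needed. The cost is that long-term statements become weaker or descriptive.
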